### Data management

Clinical data will be collected through printed CRFs, which will be stored in locked filing cabinets. Two independent research assistants who are not involved in the trial will enter the data into the electronic data management platform Yiducloud (https://www.yiducloud.com.cn/) for data imputation and check the data to monitor accuracy. All paper files and electronic documents can only be consulted by authorised researchers.

### Oversight and monitoring

The Human Research Ethics Committees review all study activities semiannually, which consists of three professors and five assistant professors who have no conflicts of interest in the study. Meanwhile, they can initiate an independent study audit at any time to ensure the quality of this study, mainly including recruitment; the accuracy, completeness, and clarity of data; attendance; adverse effects, and exercise frequency. These contents will be recorded in the shape of forms, videos, and pictures and sent to the Project Management Group (consisting of principal investigator [PI], study coordinators, coaches, a doctor or nurse with relevant disease expertise) in time. The Project Management Group will be required to give realistic feedback within four weeks. Amongst these, the PI is responsible for supervising the trial. The study coordinator is in charge of monitoring the study’s progress, such as recruitment, intervention, data fidelity, adverse effect, and providing day-to-day support for the trial. Coaches are responsible for establishing the criteria of TC. The doctor and nurse are in charge of providing safety advice and first treatment in case of adverse effects. The Trial Steering Committee consists of the statisticians, PI, the sponsor, the public, and patient representatives, which supervises the overall conduct of the trial. In addition, any information about this trial will be discussed biweekly by the Project Management Group during regular supervision meetings; if the study involves significant modifications and decisions, the Trial Steering Committee must be informed and attended. An independent Data and Safety Monitoring Board (DSMB) will be set up to review the trial data every 4 weeks to monitor data progress to ensure accuracy and safety, which consists of specialists with expertise in chronic pain clinical trials, statistical design and mind-body exercises who have no conflicts of interest in the study. Besides, we do not anticipate any major protocol amendments to this study. If this study has one, communication of significant protocol amendments within the scope of the study will be the responsibility of the PI. Information will be distributed by the project regulatory specialist or research assistant on behalf of the PI.

### Statistical analysis

The SPSS 24.0 software will be used to perform statistical analysis, and the primary outcome is the changes of LBP intensity at rest (week 12 minus baseline [week 0]). Firstly, we will compare the differences between each experimental group and the control group sequentially via using analysis of covariance (ANCOVA), adjusted for the baseline values of the VAS pain scores. The significance level of primary outcome will be set as *α* = 0.0167. If significant differences are observed amongst the three experimental groups, we will use the fixed-sequence test to compare the differences between TC group (1 session/ week) and group (5 sessions/ week); group (1 session/ week) and group (3 sessions/ week); group (3 sessions/ week) and group (5 sessions/ week) sequentially using analysis of covariance, and the significance level of fixed order test will be set as *α* = 0.05. Treatment effects with corresponding 95% confidence intervals will be presented. The intention-to-treat (ITT) will be used to analyse the primary and secondary outcomes when participants have completed randomisation and received treatment for at least 4 weeks. Then, the per-protocol (PP) analysis of the primary outcome will be used as a sensitivity analysis when participants have completed 12-week intervention and have a compliance rate of > 85%. The results of ITT and PP analysis will be compared to check the consistency of results. The missing data will be adjusted by the multiple imputation method. In addition, multivariate regression analyses will be performed to examine the effect of the TC training on the primary outcome measure, adjusting for variables in the baseline data, such as age, sex, and the level of physical activity, to verify the consistency of the results between analysis of covariance and multivariate regression analysis, and further to improve the reliability of the results. Mediation analysis will be performed through a series of linear regression models to evaluate the strength of the relationships amongst the treatment/control group, the mediator and pain outcome to identify whether baseline mindfulness of participants mediates the effect of TC on treatment outcomes.

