## Methods and analysis

### Trial design

This study is a single-centre, randomised, single-blinded (outcome assessors, data managers and the statistician), parallel controlled trial, which will be carried out in Changsha First Social Welfare Institute, Hunan Province, China. In total, 284 eligible participants with CNLBP will be randomly and equally divided into four groups in a 1:1:1:1 allocation ratio. Three experimental groups will undergo 12 weeks of supervised TC training and complete one, three or five TC sessions weekly, respectively. The control group will not receive any rehabilitation programme. Meanwhile, all participants will receive weekly health lectures until the end of the 12-week intervention and will be required to maintain a healthy lifestyle, afterwards followed by 12 weeks of follow-up after the end of the intervention.

The primary outcome (the changes of LBP intensity at rest) will be measured at baseline before randomisation and immediately after the completion of week 4, week 8, week 12 of the intervention and the end of follow-up (week 24). The secondary outcomes will be measured at baseline before randomisation and immediately after the completion of week 12 of the intervention and the end of follow-up (week 24). The details of the time schedule of this trial are shown in Table 1. The recommendations of the Consolidated Standards of Reporting Trials (CONSORT) will be strictly followed, and the protocol will be reported in line with the Standard Protocol Items (SPIRIT) [28] (Additional file 2). The flow chart is presented in Fig. 1.

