#### Baseline characteristics of trial participants

The socio-demographic information that will be collected includes gender, age, body mass index, marital status, living status, working status and education level. The clinical and CNLBP-related information that will be collected includes LBP duration, self-reported comorbidities, drug use condition (type, frequency and duration) before the start of this trial and history of back surgery.

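### Baseline variables other than pain are kept out of the ANCOVAs that decide the trial; the plan is valid, but any precision they offer is not used there

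*Protocol article*

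**What the plan says.** All of the following is in the protocol article.

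- **Comparisons with control** (Statistical analysis): each of the three Tai Chi groups is compared with control on the week-12 change in pain, "using analysis of covariance (ANCOVA), adjusted for the baseline values of the VAS pain scores", at 0.0167 each.
- **Comparisons between frequencies** (same section): 1 v 5, 1 v 3 and 3 v 5 sessions a week are tested in a fixed sequence at 0.05, also by analysis of covariance. No covariates are named for these.
- **Separate regression** (same section): a further model of the primary outcome is fitted "adjusting for variables in the baseline data, such as age, sex, and the level of physical activity". Its stated purpose is "to verify the consistency of the results between analysis of covariance and multivariate regression analysis, and further to improve the reliability of the results".
- **What is collected** (Baseline characteristics of trial participants): the socio-demographic list is "gender, age, body mass index, marital status, living status, working status and education level", and "The clinical and CNLBP-related information that will be collected includes LBP duration, self-reported comorbidities, drug use condition" among other items.
- **Baseline questionnaires** (Trial design): "The secondary outcomes will be measured at baseline before randomisation". By the Secondary outcomes section, these include the Pain Catastrophising Scale (PCS) and the mindfulness questionnaire.

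**The concern.** ANCOVA is a linear regression. The second model is the same kind of model, fitted to the same participants and outcome with more covariates. In a randomised trial both target the same mean difference, so they would be expected to agree. Agreement shows that the result is not sensitive to the covariate set, which is worth knowing, but it is not a second source of evidence.

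A covariate that predicts the outcome reduces the standard error only in the model that contains it. Here the extra variables sit in the model that decides nothing.

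What is at stake is efficiency, mainly in the between-frequency tests. Comparing frequencies is the primary objective in the Introduction, yet the Sample size section ties its alpha to the comparisons with control. In a fixed sequence, a miss on 1 v 5 also ends formal testing of the other two contrasts.

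**Working it through.** **Inputs from the documents.** Difference 2 and SD 2.2 on the 0–10 VAS; 240 evaluable participants, so 60 per arm (Sample size); alpha 0.0167 against control and 0.05 between frequencies (Statistical analysis). Tests are taken as two-sided, which the article does not state.

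**Assumptions.** R², the share of residual variance after baseline VAS that the added covariates explain, is not in the documents; 2% to 15% is shown. A between-frequency difference of 1 point is assumed. The SD of 2.2 is first taken as the residual SD after adjustment for baseline VAS.

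**The plan's own figure.** The attrition step reproduces: 60/0.85 = 70.6, so 71 per group and 4 × 71 = 284. The 240 does not follow from the stated inputs. With two-sided 0.0167 and 80% power, n = 2 × 2.2² × (2.393 + 0.842)²/2² = 25.3, so 26 per arm (27 by the t distribution), or 104 in four arms. That is a separate matter; 60 per arm is used below as stated.

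**Formulas.** SE = 2.2 × √(1 − R²) × √(2/60). Noncentrality = difference/SE. Power comes from the noncentral t with 2 × 60 − 2 = 118 degrees of freedom. Equivalent n per arm = 60/(1 − R²).

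**Result, 2.2 as residual SD**

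| R² | SE | Power, difference 2, α 0.0167 | Power, difference 1, α 0.05 | Equivalent n per arm |
|---|---|---|---|---|
| 0 | 0.402 | 99.4% | 69.5% | 60 |
| 2% | 0.398 | 99.5% | 70.3% | 61 |
| 5% | 0.391 | 99.6% | 71.7% | 63 |
| 10% | 0.381 | 99.7% | 74.0% | 67 |
| 15% | 0.370 | 99.8% | 76.4% | 71 |

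**If baseline VAS already removes part of the 2.2.** The article describes 2.2 as the SD immediately after training, not as a residual SD. With an assumed baseline correlation of 0.5, baseline VAS explains 25% of the variance and the residual SD is 2.2 × √0.75 = 1.905. Power for 1 point then starts at 81.4% and becomes 83.3%, 85.2% or 87.1% at R² of 5%, 10% or 15%.

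**Cost of four more coefficients.** The figures above ignore chance imbalance in the added covariates. With p normally distributed covariates, N participants and g groups in the model, the expected variance of a contrast is multiplied by 1 + p/(N − g − p − 1).

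- Two-group fit (N = 120): 1 + 1/116 = 1.009 with one covariate and 1 + 5/112 = 1.045 with five. The ratio is 1.036, so the added variables must explain about 1 − 1/1.036 = 3.4% to break even.
- One model on all four arms (N = 240): 1 + 1/234 = 1.004 and 1 + 5/230 = 1.022. The ratio is 1.017, with break-even at about 1.7%.

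**The case against.** The strongest reply is that nothing here is wrong. The plan prespecifies ANCOVA on the baseline value of the outcome and adds a covariate-adjusted supporting analysis. Chance imbalance under simple randomisation is already covered by the type I error of the test. A consistency check does not have to be independent evidence to be legitimate, and the proposed change keeps two models on the same data, only in the other order. All of this stands, and it is why the point is an improvement and not an error.

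Three stronger readings are tempting, and the documents do not support them.

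- *All six deciding tests adjust for baseline VAS only.* The article names that covariate for the three comparisons with control. For the between-frequency tests it names none, and a fuller document may do so.
- *The variables are known to be prognostic, so precision is certainly lost.* The Discussion speaks of catastrophising as a partial mediator and of mindfulness as linked to a better response to Tai Chi. Neither is the same as a baseline variable predicting week-12 pain beyond baseline pain. Nothing in the article calls age, sex or LBP duration prognostic, and no R² or correlation is given.
- *Every variable in the second regression is already collected.* Physical activity level is not in the article's baseline list. A condensed article may omit it, so this is not a fault, but it cannot be counted as available.

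The magnitude is also rightly challenged: it rests on an assumed R², an assumed 1-point difference and the reading of 2.2 as a residual SD.

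**Conclusion.** The point holds as an optional gain in efficiency. The deciding comparisons with control use baseline VAS alone, the between-frequency ANCOVAs have no stated covariates, and other baseline variables enter only a side analysis. There is no bias and no loss of alpha control. The claim that the second regression makes the results more reliable says more than a robustness check on the same data can deliver.

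Against control at the planned difference of 2, the gain is at most about half a percentage point. Any material gain is confined to smaller differences, chiefly between frequencies. For 1 point it is roughly 1 to 7 percentage points of power over R² of 2% to 15% (69.5% to between 70.3% and 76.4%), or about 2 to 6 points from 81.4% over R² of 5% to 15% if baseline VAS already explains a quarter of the variance. The cost of estimation reduces these figures and would cancel the gain at R² of 2% in a two-group fit. The true R² is unknown, so the benefit may be small.

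**What to change.** In the Statistical analysis section, state that all six ANCOVAs adjust for baseline VAS plus a short fixed list of variables already collected before randomisation: age, sex, LBP duration and baseline PCS total. Keep the baseline-VAS-only ANCOVA as the supporting analysis, in place of the separate regression with its open-ended list, and describe it as a check on sensitivity to covariates. Fitting one model to all four arms and taking the six contrasts from it would about halve the cost of the extra coefficients.

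The change needs a sentence or two, no new data and about four degrees of freedom. It should be fixed before anyone sees outcome data by group.

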**Methods:**

In total, 284 senior citizens with CNLBP will be recruited in this single-centre, randomised, single-blinded (outcome assessors, data managers and the statistician), parallel controlled trial. Participants will be randomly divided into either one of three TC groups (1, 3, or 5 sessions/week, on the basis of weekly health educational lectures) or weekly health educational lectures, sustaining for 12 weeks, followed by 12 weeks of follow-up after the end of intervention. The primary outcome (the changes of LBP intensity at rest) will be measured at baseline before randomisation and immediately after the completion of weeks 4, 8 and 12 of the intervention, and the end of follow-up (week 24) using the visual analogue scale (VAS, 0–10 cm) to put a mark on the VAS scale to show how severities of their average low back pain have been over the past 24 h. Secondary outcomes, including Beck Depression Inventory-II, Pain Catastrophising Scale and Five Facet Mindfulness Questionnaire, Oswestry Disability Index and Short Form-36, will be measured at baseline and immediately after the completion of week 12 of the intervention and end of follow-up. The intention-to-treat and per-protocol principles will be used to analyse outcomes with a setting at *α* = 0.05 as statistical significance.

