#### Sample size

The sample size was estimated using the PASS software (ver. 15.0). Limited studies have focused on the effect of different weekly frequencies of TC in elders with CNLBP. As such, the primary indicator was the changes of LBP intensity at rest (represented as VAS, score of 0–10). The sample size was calculated via the minimum clinically important difference of 2 on the VAS of pain intensity, and expecting the standard deviation of 2.2 immediately following TC training [33–35]. Considering the multiple comparison, the Bonferroni adjustment was applied, a sample with 240 participants was needed with a power of 80% and an alpha of 0.05 (*α*=0.05 is the overall allowable type I error in the comparisons between each experimental group and the control group sequentially). Moreover, considering a 15% attrition rate, at least 71 participants per group will be needed in this protocol trial [Total participants: 240/ (1−0.15) ≈ 284 participants, considering an equal allocation of 1:1:1:1 to four groups].

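### Holm's step-down could replace the fixed 0.0167 for the three Tai Chi-versus-control tests: same 5% error, never fewer rejections, but a material gain only if the once-weekly effect is well below 2 cm

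*Protocol article*

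**What the plan says.** Under Statistical analysis, each Tai Chi arm is compared with control by ANCOVA on the week-12 change in resting pain, adjusted for baseline VAS. The section then fixes one threshold: "The significance level of primary outcome will be set as" 0.0167.

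The Sample size section gives the reason: "Considering the multiple comparison, the Bonferroni adjustment was applied". It describes 0.05 as the level that "is the overall allowable type I error in the comparisons between each experimental group and the control group sequentially". Since 0.05/3 = 0.0167, the two sections agree.

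Both sections say the comparisons are made sequentially, but neither lets the threshold change after a rejection. The only procedure in which order matters is the fixed-sequence test at 0.05, and that is reserved for the later comparisons between Tai Chi arms.

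The design effect is "the minimum clinically important difference of 2 on the VAS of pain intensity", with SD 2.2. It is used for all arms, and no separate effect is given for any one frequency.

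**The concern.** With a single-step Bonferroni rule, the second and third comparisons stay at 0.0167 even after the first has been rejected. Once one null hypothesis is rejected, only two remain, so part of the 5% goes unused. The arm with the smallest true effect bears most of that cost.

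In this trial that arm may matter. The Introduction hypothesises that five sessions a week does better than one or three, and the Discussion says the trial will look for the lowest frequency that works. If benefit does rise with frequency, once weekly is the natural candidate for the smallest effect. A missed difference from control there would make the required frequency look higher than it is.

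**Working it through.** **Inputs from the protocol.** Overall alpha 0.05 and 0.0167 per comparison; difference 2, SD 2.2, power 80%; 240 evaluable participants in four equal arms, so 60 per arm; 15% attrition.

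**Assumptions.** Two-sided tests (the protocol does not state sidedness); normal tests with a shared control arm; 2.2 as the SD of the analysed outcome; no precision gain from ANCOVA unless stated. All unequal effects below are assumed.

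**1. The protocol's own figure.** "a sample with 240 participants was needed with a power of 80"% is the stated size. From the stated inputs, n per arm = 2 × 2.2² × (2.394 + 0.842)² / 2² = 25.3, so 26 per arm, or 104 in total (27 and 108 with the t distribution). The 240 is not reproduced. The attrition step is: 60/0.85 = 70.6, so 71 per arm and 284 in total. I take 60 per arm as given. It explains why power at the design effect is so high.

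**2. Power for one comparison at 60 per arm.** The standard error is 2.2 × √(2/60) = 0.4017. Power ≈ Φ(effect/0.4017 − z), with z = 2.394 at 0.0167 and 1.960 at 0.05. The second figure is a ceiling for Holm: the power the weakest arm would have if the other two were certain to be rejected first.

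- 2.0 cm: Φ(4.979 − 2.394) = 99.5%; ceiling Φ(4.979 − 1.960) = 99.9%
- 1.5 cm: Φ(3.734 − 2.394) = 91.0%; ceiling Φ(3.734 − 1.960) = 96.2%
- 1.0 cm: Φ(2.490 − 2.394) = 53.8%; ceiling Φ(2.490 − 1.960) = 70.2%
- 0.8 cm: Φ(1.992 − 2.394) = 34.4%; ceiling Φ(1.992 − 1.960) = 51.3%

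**3. The actual Holm procedure.** The other arms are not certain to be rejected, so Holm was simulated with three tests sharing one control arm, at least 300,000 replicates per setting.

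| True effects at 1/3/5 sessions (cm) | Once-weekly, Bonferroni | Once-weekly, Holm |
|---|---|---|
| 2.0/2.0/2.0 | 99.5% | 99.8% |
| 1.5/2.0/2.5 | 91% | 96% |
| 1.0/1.5/2.0 | 54% | 69.5% |
| 0.8/1.2/1.6 | 34% | 49% |

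At 1.0/1.5/2.0 cm the chance that all three arms are significant goes from 52% to 69%. With 71 per arm, once-weekly power there goes from 62% to 77%. With the other two arms held at 2 cm, the gain peaks at about 16 points for a weakest-arm effect of 0.75 to 1.0 cm.

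**4. Familywise error under Holm, 60 per arm.** 4.5% with all three nulls true, 4.6% with two true, 4.9% with one true. It stays within 5%.

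**5. Sensitivity to the SD.** With an assumed baseline correlation r, ANCOVA reduces the SD to 2.2 × √(1 − r²). At r = 0.5 this is 1.91, and once-weekly power at 1.0/1.5/2.0 cm is 68% versus 82%. At r = 0.6 it is 1.76, and power is 76% versus 87%. The gain falls from about 16 points to 13 and 11. In the other direction, if 2.2 were a single-visit SD and the change-score SD were 2.2 × √2 = 3.1 with no baseline gain, power per arm at 2 cm everywhere would be 87% versus 92%.

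**The case against.** The strongest reply is that nothing here is broken. The two sections agree, the rule is prespecified and the error is controlled. On the protocol's own 2 cm and SD 2.2, Holm adds about 0.3 points. The hypothesis in the Introduction ranks the frequencies but does not put once weekly below 2 cm. A gradient alone costs little: at 2.0/2.5/3.0 cm once-weekly power is 99.5% versus 99.9%. The large gains need an effect of about half the stated minimum important difference, and detecting such an effect may not identify a useful frequency. Other procedures, such as step-down Dunnett, would also serve. Bonferroni also has simple matching simultaneous intervals.

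Most of this stands. It rules out two stronger readings that a reader might infer. One is that the fixed 0.0167 is a statistical error; it is not. The other is that Holm recovers substantial power for the weakest arm in any case. The documents do not support that, because they give no arm-specific effects and the only effect they state leaves almost nothing to recover.

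Two parts carry less weight. The ANCOVA tests for any difference from control, not for one of 2 cm, so power below 2 cm still bears on what the trial will report. And the plan already presents 95% intervals beside tests at 0.0167, so it does not use the simultaneous intervals that Bonferroni would offer.

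**Conclusion.** The point holds as an optional efficiency improvement. Holm keeps the same 5% familywise error as the planned rule, rejects everything that rule rejects and sometimes more, and needs no added assumption.

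The size is conditional. The once-weekly gain is negligible at the protocol's uniform 2 cm, about 5 points if that arm truly gains 1.5 cm, and about 15 to 16 points at 0.8 to 1.0 cm before baseline adjustment. These figures rest on 60 evaluable per arm, SD 2.2, two-sided testing and assumed effects. The change is therefore worth most if benefit falls with lower frequency, as the trial's hypothesis allows, and the once-weekly effect is well below 2 cm.

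**What to change.** Before unblinding, replace the fixed 0.0167 under Statistical analysis with a sentence saying that the three Tai Chi-versus-control p-values are tested by Holm's step-down procedure at overall two-sided alpha 0.05: smallest against 0.0167, next against 0.025, largest against 0.05, stopping at the first non-rejection. The comparisons between Tai Chi arms can stay as written.

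This costs one sentence, with no extra data and no change in sample size. The small downside is that simultaneous confidence intervals matching Holm are less simple than Bonferroni intervals, so the text should say whether the reported 95% intervals are unadjusted. Keeping Bonferroni would remain defensible.

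### The three Tai Chi versus control contrasts are tested at 0.0167, but the 95% intervals promised for treatment effects do not match that test (minor)

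*Protocol article*

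**What the plan says.** Under Sample size, the protocol article states "Considering the multiple comparison, the Bonferroni adjustment was applied" and defines 0.05 as the total type I error allowed over the comparisons of the experimental groups with control.

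Under Statistical analysis, these comparisons come first and use ANCOVA adjusted for baseline VAS. For them the article says "The significance level of primary outcome will be set as *α* = 0.0167". The TC groups are then compared with one another in a fixed sequence, for which "the significance level of fixed order test will be set as *α* = 0.05".

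The next sentence reads "Treatment effects with corresponding 95% confidence intervals will be presented". It is not limited to either set of contrasts. The article mentions no other interval level, and it does not say that the intervals are unadjusted or descriptive.

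**The concern.** The article fixes both a test level and an interval level, and for the three control contrasts the two do not belong together. A 95% interval excludes zero when two-sided p is below 0.05, whereas the decision needs p below 0.0167. For any p between these values, the interval and the decision give different messages.

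The disagreement runs one way only: the interval looks favourable while the test is not significant. The abstract names only 0.05 as the significance level, so a reader could easily take a 95% interval that excludes zero as a positive result. The Discussion says the trial will look for the lowest frequency that works. A modest effect in the once-weekly group is where a borderline result could arise, and the report would then carry two readings of one primary contrast with no rule for which to stress.

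**Working it through.** **Inputs.** From Statistical analysis: test level 0.0167 for the control contrasts and interval level 95%. From Sample size: overall error 0.05, SD 2.2, planned difference 2, and 240 evaluable participants, that is 240/4 = 60 per arm. Assumed: two-sided testing (the article does not state sidedness), a normal approximation, and an unadjusted two-group standard error.

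**The plan's own figure.** Bonferroni for three contrasts: 0.05/3 = 0.01667, which rounds to the stated 0.0167. It reproduces.

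**Matching interval level.** 1 − 0.05/3 = 0.9833, so 98.33%. The critical value is 2.394 instead of 1.960. The ratio 2.394/1.960 = 1.22, so the matching interval is 22% wider whatever the standard error.

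**Where the two disagree.** SE = 2.2 × √(2/60) = 0.402.

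| Interval | Half-width (cm) |
|---|---|
| 95% | 1.960 × 0.402 = 0.79 |
| 98.33% | 2.394 × 0.402 = 0.96 |

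An observed difference between 0.79 and 0.96 cm in absolute size has a 95% interval excluding zero and fails the 0.0167 test. If all 71 randomised per arm were analysed with complete information, SE = 2.2 × √(2/71) = 0.369 and the band would be 0.72 to 0.88 cm.

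**Example (60 per arm).** For a difference of 0.88 cm, z = 0.88/0.402 = 2.19 and p = 0.028. The 95% interval is 0.09 to 1.67, which excludes zero. The 98.33% interval is −0.08 to 1.84, which agrees with the test.

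**How often, per contrast.** The probability is P(|Z| > 1.960) − P(|Z| > 2.393), where Z has mean (true difference)/0.402 and variance 1, and 2.393 is the critical value at the stated 0.0167.

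| True difference (cm) | Chance of disagreement |
|---|---|
| 0 | 0.05 − 0.0167 = 3.3% |
| 0.5 | 11% |
| 0.88 | 17% |
| 1 | 16% |
| 1.5 | 5% |
| 2 (planned) | 0.4% |

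**Three contrasts together.** By simulation with a shared control arm (correlation 0.5 between contrasts), under the global null at least one of the three disagrees about 9% of the time. At least one of three 95% intervals misses its true value about 12.5% of the time, against about 4.4% with 98.33% intervals.

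**The case against.** The case against has five parts.

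- **The decision rule is clear.** The 0.0167 level is fixed, and nothing makes the interval a decision criterion. This stands: no test result under the plan changes.
- **Marginal 95% intervals are legitimate beside adjusted tests.** This also stands. A reader might infer that the primary intervals are too narrow, or that they break a promise of joint 95% coverage. The article does not support that. Each 95% interval has its nominal coverage for its own contrast, and the plan never claims simultaneous coverage, so the 12.5% figure contradicts no statement in it.
- **The sentence may concern only the TC versus TC tests.** It follows directly after the 0.05 fixed-sequence level, which 95% does match. This is possible but not persuasive. The wording has no limit, and the control contrasts are the main treatment effects: they are tested first and the sample size is built on them. If only the later contrasts were meant, the primary ones would have no stated interval level and would need the same clarification.
- **A separate analysis plan may settle it.** Labelling of intervals is often left there. But the article itself states both levels, so the point is a mismatch in the text and not an omission.
- **The consequence is small.** This stands. The band lies below half of the "minimum clinically important difference of 2 on the VAS of pain intensity". At its top edge the upper limit is 0.96 + 0.79 = 1.75 for the 95% interval and 0.96 + 0.96 = 1.92 for the 98.33% interval. Both are below 2, so a reader judging against that threshold reaches the same view with either.

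**Conclusion.** The point holds as a minor reporting inconsistency: the interval level stated for treatment effects does not match the test level set for the three primary contrasts. A reader might go further and infer that type I error is inflated. It is not, because the tests at 0.0167 hold the overall 0.05 for the control comparisons whatever intervals are printed beside them.

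The chance of a visible contradiction is about 3% per contrast under the null and 0.4% at the planned difference. It reaches about 17% only if the true effect lies near 0.88 cm.

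The figures in cm are illustrative. They rest on SD 2.2, 60 per arm and an unadjusted standard error. Baseline-adjusted ANCOVA would normally shrink the standard error, and the band from 1.960 to 2.394 standard errors shrinks with it. The mismatch and the 22% ratio do not depend on these inputs. They do assume two-sided testing. A one-sided test at 0.0167 would match a two-sided interval of 1 − 2 × 0.0167 = 96.67%, so 95% would still not correspond.

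**What to change.** Replace the interval sentence before unblinding with wording such as:

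> The week 12 differences between each TC group and control will be reported with 98.33% confidence intervals, matching the 0.0167 test. If 95% intervals are also or instead shown for these contrasts, they will be labelled as unadjusted for multiplicity and will not be used for the decision. Contrasts between TC groups tested at 0.05 will carry 95% intervals.

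State sidedness in the same place; the 98.33% level assumes two-sided tests. The change needs no new data, no extra participants and no alteration to the tests. Its downside is that the primary intervals become about 22% wider (0.96 instead of 0.79 cm half-width in the illustration). If the sponsor prefers to show only 95% intervals, the label alone removes the ambiguity.
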